## **Interventions**

### *Briefing Session*

All project participants enrolling in the project will have to attend a briefing session (Figure 1).

The briefing session will be a facilitated learning session based around self-management and lifestyle modification. Education sessions and problem solving will be developed and carried out using the Self Determination Theory (SDT) framework [37]. This theory is used to support, educate and motivate participants around positive lifestyle choices, as well as the empowerment of individuals over their health care [37]. SDT reflects that an individual's on-going functioning is a product of a continuous interaction between cognitive, behavioural, and contextual factors, and more than a matter of education by itself [37]. Classroom learning for example is shaped by factors within the academic environment, but particularly by the reinforcements experienced by individuals and by others [37]. To adhere to this framework, participants will be encouraged to participate actively in the briefing sessions through group and task orientated learning, and education will be delivered through case studies to stimulate vicarious learning [37]. Participants will be exposed to real life scenarios of health risk modification and given brief tasks to stimulate this thought process. SDT has been chosen as the framework in which to deliver the briefing session as has been shown to complement MI and CBT integration [37]. The briefing sessions will be facilitated by a member of the project team who is registered healthcare practitioner through the Australian Health Practitioner Regulating Authority (AHPRA). The sessions will also include a guest speaker representing the community health programs.

### *Intervention*

The intervention group will receive the blend of MI and CBT. This model of patient-centred self-management support, delivered as an office-based program through telephone calls has demonstrated successful outcomes for similar populations [19,22,38-9]. A member of the project

team will facilitate the MI/CBT intervention via the telephone. The individual who will deliver the telephone support is a registered healthcare practitioner through the Australian Health Practitioner Regulating Authority (APHRA). He has attended a 2-day workshop on MI and has received additional coaching from [name] [name], who is a nationally endorsed Health Psychologist and Sport and Exercise Psychologist who has been registered and practicing as a Psychologist since 1998. The individual who will deliver the intervention also delivered 144 hours of MI-CBT during the H4U trial.

Each participant will receive 5 phone calls, each lasting up to 20 minutes. Telephone support following a CBT approach, bedded in MI philosophy has shown to be effective in behaviour modification [38-9]. Participants will receive 4 calls over a 6-week period, with a 'booster' call at 12 weeks. In terms of incorporating the MI/CBT blend, MI will be utilised for sessions 1 to 3, as MI is identified as an effective tool for behaviour change initiation [21]. From session 3 to session 5 a blend of MI/CBT will be used, as CBT is an action orientated treatment [21, 23-4].

As part of self-management support, participants, where the intervention is appropriate, will be made aware of programs aimed at lifestyle risk modification existing in the community. Following the MI/CBT theory, no mandatory referrals will be made to these programs, however the facilitator may highlight the existence of these programs should the situation warrant it. The facilitators will be aware of the programs that are available in the community and can make appropriate referral to the programs on behalf of the participants. This pathway may highlight to participants the range of programs that are available in the community. Utilizing existing programs in the community may be of benefit to the participants, while it also encourages service co-ordination and avoidance of service duplication.

*Control*

242 All control group participants will attend the briefing session so they will receive the same  
243 educational material around lifestyle risk factor modification as group 1 from that session.

244 Participants of the control group will be contacted to enquire about their attendance at the  
245 follow-up session, reminding them about the requirement for outcome measure completion.  
246 Apart from this contact participants the control group will receive no further routine contact  
247 initiated by the project team.

### 248 **Intervention Fidelity**

249 To assist with improving the credibility of evidence resulting from behaviour change studies the  
250 reporting on treatment fidelity has been recommended [40]. Assessments in intervention fidelity  
251 are integral to intervention research but few published trials report these processes in detail  
252 [41]. This methodological shortcoming makes it very difficult to distinguish between the quality of  
253 behaviour change interventions, and, consequently, to be able to establish whether MI provision  
254 has contributed to any intervention effects [41]. Treatment fidelity has been defined as the  
255 “methodological strategies used to monitor and enhance the reliability and validity of  
256 behavioural interventions” [41]. To measure the fidelity of the treatment the Motivational  
257 Interviewing Treatment Integrity code will be used [42].

258 For measurement of fidelity 10% of counselling sessions in the study will be digitally recorded.  
259 The recorded sessions will be assessed for adherence to MI principles using the Motivational  
260 Interviewing Treatment Integrity code [26] by an expert independent coding group. Coders are  
261 blind to the study arm of the session and the study hypotheses. We anticipate that MI sessions  
262 will receive scores of 4 or higher on the 1–5 global rating. With respect to frequency measures  
263 of counsellor behaviour we expect MI sessions to have a higher reflection to question ratio and  
264 significantly fewer instances of giving information.

### 265 **Study Outcomes**

The primary endpoint is a change in physical activity levels, measured at 3 points- baseline, 13-weeks, and at 9 months (Table 1). Secondary endpoints include a change in self-efficacy, quality of life, waist circumference, BMI, and smoking status (Table 1.)

### *Physical Activity*

The primary endpoint is a change in physical activity levels. Physical activity will be measured objectively using an accelerometer (ActiGraph, Florida, United States) and a log diary to document the type of activity completed, and any occasions when the accelerometer was removed.

The ActiGraph GT3X+ is a validated, tri-axial activity monitor that provides data on physical activity including activity counts, steps and activity intensity (METs) [43]. The output from the tri-axial accelerometer measures time spent in physical activity using standard cut-off points for sedentary, light, moderate, vigorous and very vigorous physical activity. The primary outcome measure will be minutes of physical activity at moderate intensity or greater per week.

The research team will explain to the participant how to wear the accelerometer, requesting it to be worn from waking in the morning until going to bed at night. Participants will be asked to remove the ActiGraph when they are showering, bathing or swimming. After seven days of wearing the accelerometer, the accelerometers will be collected at the next possible visit to the hospital or arrangement will be made for collection from participants at a location most convenient to them.

### *Self-Efficacy*

Self-Efficacy to be physically active will be measured via a physical activity self-efficacy survey. This survey has been built upon previous research, with modifications to suit the target group that this study proposes [44]. The survey measures confidence related to completing physical activity while faced with recognised barriers to physical activity completion.

290 *Medical Outcomes Study Short Form 12 Health Survey (SF-12)*

291 To measure quality of life the Medical Outcomes Study Short Form 12 Health Survey (SF-12)  
292 will be used [49]. The SF-12 was derived from twelve questions of the SF-36, which make up  
293 the MCS (Mental Component Summary) and PCS (Physical Component Summary). The survey  
294 can be administered in two to three minutes, which saves both time and resources in large-  
295 scale population surveys. The SF-36 has been validated in an Australian population 3. The two  
296 scores range between 0 and 100, with increasing values equating to better health.

297 Using the SF-12 also allows for conversion to utility scores which can also facilitate the  
298 undertaking of an economic analysis.

299

**Table 1. Primary and secondary outcome measures**

| Primary and secondary outcome measures                                                                                                                                                                                                                                                                                              |
|-------------------------------------------------------------------------------------------------------------------------------------------------------------------------------------------------------------------------------------------------------------------------------------------------------------------------------------|
| Primary 

Physical Activity – ActiGraph [43]

                                                                                                                                                                                                                                          |
| Secondary 

Self-Efficacy- Modified physical activity self-efficacy survey [44]

Quality of Life: SF-12 Survey [49]

Waist Circumference- within AUSDRISK tool [50]

Smoking- within AUSDRISK tool [50]

Nutrition- within AUSDRISK tool [50]

BMI

 |

**Sample Size and Statistical Analysis**

To compare differences in our outcome measures a series of 3 x 2 mixed model ANOVAs will be undertaken. Utilizing data from the H4U study, to detect an effect size of 0.35 or greater, with the alpha set at .05, and the power set at .90, a sample size of 50 participants per arm will be required. Protecting against a drop-out rate of 20% over the 9 month period, 68 participants will be recruited and randomized into each arm. The study therefore aims to recruit approximately 136 participants.

A full intention-to-treat principle will be used. For participants with missing data at 3 month and 9 month the last-observation-carried forward approach will be adopted (Shao and Zhong, 2003). Repeat sensitivity analyses will be undertaken to provide indication that the imputed values have a significant effect on the outcome.

313

314 **Process measures**

315 The project team will log the number of referrals made by the surgeons in Specialist Clinic. The  
316 project team will record patient feedback regarding interest and opinions on the project, which is  
317 hoped may give insight into future program development strategies.

318 A log will be maintained of how many project participants contact the project team during the  
319 intervention phase, the reason for contact, the method of contact and the outcome. During any  
320 non-structured contact no intervention is to be delivered at that time.

321 To examine the acceptability of the H4U study, participants allocated to the intervention group  
322 will also be administered an additional questionnaire, after the 9 months follow up. This  
323 questionnaire will include items addressing satisfaction with the components of the project, their  
324 perceived utility of the intervention. The questionnaire will also address whether participants  
325 attended a community health program, and the frequency of visits. To obtain a more in-depth  
326 understanding of the potential barriers and facilitators at the service delivery and individual level  
327 to uptake of this programme, we will also conduct semi structured interviews with a subsample  
328 of participants in the intervention group. Recruitment for the interviews will be purposive to  
329 maximise variation such as urban/rural location, gender and age for patients. Sampling will  
330 continue until no new themes or categories emerge from the data (the so-called thematic  
331 saturation) [31]. The interviews will be conducted face-to-face or by telephone by a project  
332 officer with experience in qualitative interviews. Participants will be asked about their  
333 satisfaction with the program, whether they perceived it to be effective, what they liked or  
334 disliked, and their perception of the content. Interviews will be digitally recorded and transcribed.  
335 Interview transcripts and socio-demographic data will be entered as a project in NVIVO (QSR  
336 NVIVO7, Doncaster, Australia), a program for managing and analysing qualitative data. The

NVIVO software enables multilevel coding of text against a set of identified analytical categories. The study team will use an iterative process to understand the themes and key issues arising from the data.

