Patients have stated that they would like, and to some extent expect the healthcare system to provide some guidance on lifestyle behaviour change and physical activity (PA) [12]. Doctors practicing in hospitals have stated that they do not have sufficient time to spend with patients giving advice on preventive measures [13]. The working intensity of doctors make it difficult to spend sufficient time with patients discussing preventive health [13]. Unpublished data from Bendigo Health supports this, with doctors indicating that discussions about smoking, nutrition and physical activity (SNAP) health risk factors are very important for health, yet, at the same time they are not a high priority. This has resulted in low implementation rates of preventative health practices.

The H4U study demonstrated that integrated motivational interviewing (MI) and cognitive behaviour therapy (CBT) resulted in significant changes in physical activity and health related outcomes for secondary care participants. The H4U-2 extends the H4U study in a number of ways including: (i) increased focus of the intervention on maintenance of behaviour change; (ii) a longer follow-up timeframe to test the maintenance effect of the intervention; decrease in intervention number from 8 sessions to 5; and (iii) referrals by surgeons into the program. The H4U-2 offers surgeons a pathway to integrate preventive health into clinical care, delivering a brief intervention to at risk patients, and referring the patient in an efficient manner to a dedicated resource.

The primary objective of this study is to determine the effectiveness of lifestyle intervention in secondary care patients presenting to a non-admitted elective clinic in a public hospital who do not participate in enough physical activity to be deemed sufficiently physically active. Secondary aims relate to the effect of the MI/CBT intervention on self-efficacy, quality of life, and anthropometric measures. In addition, this study will investigate the acceptability, feasibility cost-effectiveness of delivering the telephone intervention in this setting.

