## **METHODS AND ANALYSIS**

### **Design**

The H4U-2 project is a randomised controlled trial with assessment of outcomes at three points- baseline, post 12 weeks and 9 months designed and reported in line with the CONSORT recommendations for reporting (Figure 1). The study will be conducted at large regional tertiary public hospital that's serves a wide geographical region, with a socioeconomically diverse population. A total of 136 patients who present to BH Specialist Clinic as an elective admission will be recruited and included in the project (figure 1). The trial will be registered with the Australian and New Zealand Clinical Trials Registry prior to patient recruitment. The study will commence 01/12/18 and commence 01/12/22.

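### No primary time point or contrast is named, and the three-visit, two-group ANOVA does not by itself show whether an effect is maintained at 9 months

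*Protocol*

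**What the plan says.** The section Sample Size and Statistical Analysis gives one between-group method for all outcomes: "To compare differences in our outcome measures a series of 3 x 2 mixed model ANOVAs will be undertaken". It names no term of the ANOVA and no contrast.

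Study Outcomes defines the endpoint: "The primary endpoint is a change in physical activity levels, measured at 3 points- baseline, 13-weeks, and at 9 months". The Design section gives the same schedule: "assessment of outcomes at three points- baseline, post 12 weeks and 9 months". The Physical Activity section names the variable but no visit: "The primary outcome measure will be minutes of physical activity at moderate intensity or greater per week".

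The Background lists, among the ways this trial extends its predecessor, "a longer follow-up timeframe to test the maintenance effect of the intervention".

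The secondary endpoints in Study Outcomes include "quality of life, waist circumference, BMI, and smoking status", and the ANOVA sentence makes no exception for any of them.

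**The concern.** The three-level factor can only be the three visits, so baseline is one level of the response. Randomisation makes the expected between-arm difference at baseline zero. A test over all three visits asks whether the arms differ in their pattern over time. It does not ask whether they differ at 9 months.

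The longer follow-up was added to learn about maintenance. A significant omnibus result could arise from an effect that lasts or from one that has gone by 9 months, and the plan does not say which comparison settles the matter. The primary time point is part of the endpoint definition and belongs in the protocol.

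Two smaller matters follow from the same sentence. Using baseline as a response gives up precision that a baseline covariate would supply. And a mixed ANOVA is not a suitable method for smoking status, which is categorical.

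**Working it through.** **Inputs.** From the protocol: two arms, three visits, alpha 0.05, effect size 0.35 ("to detect an effect size of 0.35 or greater"), 50 per arm before drop-out and 68 per arm randomised. Assumed, because the protocol does not give them: equal variances and one common correlation rho between visits (compound symmetry), rho = 0.3, 0.5 and 0.7; two-sided tests; 0.35 read as a standardised mean difference d. Group differences are in SD units, ordered baseline, first follow-up, 9 months.

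**The plan's own figure.** The 50 per arm cannot be tied to a particular test, because neither the effect-size metric nor the tested term is stated. A two-sample comparison at 90% power needs 172 per arm (normal approximation) if 0.35 is d, and 44 if it is Cohen's f. What follows does not depend on settling that.

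**Group-by-time test.** Noncentrality is lambda = (n/2) × SS / (1 − rho), with n per arm, SS the sum of squares of the three group differences about their mean, and 2 and 2(2n − 2) degrees of freedom.

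- Maintained (0, d, d): mean 2d/3, SS = (4/9 + 1/9 + 1/9)d² = 2d²/3.
- Lost (0, d, 0): mean d/3, SS = (1/9 + 4/9 + 1/9)d² = 2d²/3.
- Half maintained (0, d, d/2): mean d/2, SS = (1/4 + 1/4 + 0)d² = d²/2.

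The first two are equal for any d, n and rho. At d = 0.35, n = 50, rho = 0.5: SS = 2 × 0.1225/3 = 0.0817, lambda = 25 × 0.0817/0.5 = 4.08, power 0.42.

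| rho | Power, 50 per arm, maintained or lost | Power, 68 per arm, maintained or lost |
|---|---|---|
| 0.3 | 0.31 | 0.41 |
| 0.5 | 0.42 | 0.54 |
| 0.7 | 0.64 | 0.78 |

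A half-maintained effect has less power than a complete loss: 0.32 against 0.42 at rho 0.5 and 50 per arm. If 0.35 is Cohen's f, so that d = 2 × 0.35 = 0.70, lambda is 16.33 and power is 0.96 for both the maintained and the lost pattern (rho 0.5, 50 per arm).

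**Check by simulation** (10,000 runs, 50 per arm, d = 0.35). With common rho 0.6, power is 0.51 for both patterns. With correlations of 0.7 between adjacent visits and 0.5 between baseline and 9 months, power is 0.53 maintained and 0.59 lost, so the equality fails in the direction of the lost effect.

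**Group main effect.** lambda = (n/2) × (mean difference)² / ((1 + 2rho)/3). At n = 50, rho = 0.5, d = 0.35:

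- Maintained: mean 0.233, lambda = 25 × 0.0544/0.667 = 2.04, power 0.29.
- Lost: mean 0.117, lambda = 25 × 0.0136/0.667 = 0.51, power 0.11.

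This term separates the patterns, but the zero at baseline pulls both means down.

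**Baseline as covariate.** In units of SD², a 9-month change from baseline has variance 2(1 − rho), and a baseline-adjusted 9-month value has 1 − rho². The ratio is (1 + rho)/2. Power of the two-sided t test at d = 0.35, 50 per arm:

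| rho | Variance ratio | Change from baseline | Baseline-adjusted |
|---|---|---|---|
| 0.3 | 0.65 | 0.31 | 0.44 |
| 0.5 | 0.75 | 0.41 | 0.52 |
| 0.7 | 0.85 | 0.61 | 0.68 |

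**The case against.** The protocol never says that the interaction is the test. It names no term, and it excludes no follow-up contrasts. An analysis plan that is not shown may choose the term and add contrasts by visit, the order of testing and covariates; their absence here is not an error. A 3 x 2 layout also yields means by visit, which would show whether an effect lasted. All of this stands. A reader might infer that the planned analysis cannot tell maintenance from relapse at all, and the documents do not support that. The equality belongs to the omnibus interaction alone and is exact only under compound symmetry.

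The stated primary objective is effectiveness, and maintenance appears as an extension of the earlier study, so an endpoint covering both follow-ups is understandable. This means that 9 months is a well-supported choice and not a dictated one.

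A baseline measured as a response is valid in a randomised trial. The gain from adjustment is one of efficiency, and the comparison above is with a change-from-baseline contrast, which the protocol does not specify.

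Under full intention to treat with last observation carried forward, 68 per arm would be analysed rather than 50. Both are shown; the figures for 68 ignore any distortion from carrying values forward.

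One part of the point is not answered by these objections. The primary time point belongs to the endpoint definition, and the protocol fills that place with three visits, one of which precedes treatment.

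**Conclusion.** The point holds in limited form. The protocol fixes a primary endpoint over three visits including baseline, applies a 3 x 2 mixed ANOVA to it, and names no primary time point or contrast. A significant group-by-time result would not by itself show that an effect is maintained: its noncentrality is identical for a fully kept and a fully lost effect under compound symmetry, and in the one decaying-correlation case examined it was more sensitive to the lost effect. Power at d = 0.35 ranges from 0.31 to 0.64 (50 per arm) and from 0.41 to 0.78 (68 per arm) for rho from 0.3 to 0.7. These values rest on an assumed rho and on reading 0.35 as d; the equality of the two patterns rests on neither.

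Baseline as response is a loss of precision and not a bias. ANOVA for smoking status is a wrongly stated method, but it concerns one secondary outcome and adds little weight. The change should be made; the point does not mean that the trial's data could not answer the maintenance question.

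**What to change.** In Study Outcomes and in Sample Size and Statistical Analysis:

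- Name one primary time point. Nine months fits the maintenance aim in the Background; the sponsor may justify another.
- Define the primary analysis as the between-arm difference in weekly minutes of moderate-or-greater activity at that visit, from a linear mixed model on the follow-up visits with baseline activity as covariate and arm by visit. Report the other visit's contrast as a secondary result.
- Use the same model for the continuous secondary outcomes. For smoking status use a categorical method: a logistic GEE or mixed model, or a simple tabulation.
- Tie the sample-size statement to the chosen contrast, and state the metric of the effect size and the assumed correlation.

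The cost is protocol wording; no extra data or visits are needed. The small downside is that an effect seen only at the other visit becomes a secondary claim.

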## **CONCLUSION**

The H4U-2 study will evaluate an innovative means of increasing physical activity in patients attending a non-admitted elective clinic in a public hospital who are deemed insufficiently physically active. The Healthy 4U-2 study builds upon the recommendations of the Healthy 4U study, incorporating a longer follow-up time to assess maintenance of behaviour change, as well as undertaking a more robust economic analysis. Due to the positive results of the Healthy 4U study the Healthy 4U-2 study will decrease the number of intervention sessions from 8 sessions to 5 sessions. The H4U-2 study has potential as a cost-effective home office based intervention

385 for physical activity uptake. The effectiveness of the intervention can be demonstrated in a  
386 rigorously conducted clinical trial.

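### Last observation carried forward as the main missing-data rule can bias the 9-month arm difference, up or down, even when drop-out is completely random

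*Protocol*

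**What the plan says.** The Protocol, Sample Size and Statistical Analysis, fixes three things together:

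- Population: "A full intention-to-treat principle will be used".
- Missing follow-up values: "For participants with missing data at 3 month and 9 month the last-observation-carried forward approach will be adopted".
- Test: "a series of 3 x 2 mixed model ANOVAs will be undertaken".

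One further sentence promises a check: "Repeat sensitivity analyses will be undertaken to provide indication that the imputed values have a significant effect on the outcome".

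The purpose of the late visit is stated twice. The Background lists, among the extensions of the preceding study, "a longer follow-up timeframe to test the maintenance effect of the intervention", and the Conclusion describes the trial as "incorporating a longer follow-up time to assess maintenance of behaviour change". Study Outcomes makes 9 months one of the time points of the primary endpoint: "The primary endpoint is a change in physical activity levels, measured at 3 points- baseline, 13-weeks, and at 9 months". Under Interventions, "Participants will receive 4 calls over a 6-week period", and the last planned call is a booster at 12 weeks. No intervention call is planned between then and 9 months.

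The first follow-up is called 12 weeks, 13 weeks and 3 months in different places. I read these as one visit and call it week 12.

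**The concern.** The 9-month measurement asks what happens to activity once contact has stopped. For anyone with a week-12 value and no 9-month value, the rule answers by assumption: nothing changed. For anyone lost before week 12 it makes a different assumption, that the person is still at baseline.

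Neither assumption is neutral for the 9-month comparison. The first can show maintenance that did not occur, and the second can dilute maintenance that did. Which one dominates depends on features of the trial that cannot be known in advance. The rule is written into the protocol as the main method, so it is not a detail left for a statistical analysis plan to supply.

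**Working it through.** **Inputs from the protocol.** 68 per arm; drop-out of 20% over 9 months; an effect size of 0.35 whose metric is not stated. At 20%, 0.20 × 68 = 13.6, so about 14 per arm (27 of 136) would have an imputed 9-month value. The protocol gives no figure for the effect of imputation, so there is none to reproduce.

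**Assumptions.** Drop-out is equal in both arms and completely random. The protocol does not say how loss divides before and after week 12, so both extremes and an even split are shown. The week-12 difference is taken as 0.35 SD (0.35 read as a standardised difference) or 0.70 SD (0.35 read as Cohen's f for two equal groups, d = 2f).

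**Formula.** Let D12 be the week-12 difference, R the share of it truly kept at 9 months, p the share of each arm lost after week 12, and q the share lost before week 12. Those still observed contribute R·D12, late losses contribute D12, and early losses contribute zero because they carry randomised baseline values:

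LOCF difference = (1 − p − q)·R·D12 + p·D12

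Bias = p(1 − R)·D12 − q·R·D12

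The first term is the late-loss bias and vanishes if nothing fades (R = 1). The second is the early-loss bias and vanishes if nothing is kept (R = 0). They cancel when p(1 − R) = qR, for example p = q with R = 0.5.

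**Numbers.** Simulation: correlation 0.5 between visits, baseline-adjusted (ANCOVA) contrast at 9 months, two-sided 5% level.

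| D12 (SD) | R | p late | q early | True 9-month effect | LOCF by formula | LOCF simulated | Rejection |
|---|---|---|---|---|---|---|---|
| 0.35 | 0 | 0.20 | 0 | 0 | 0.07 | – | 7.9% |
| 0.70 | 0 | 0.20 | 0 | 0 | 0.14 | 0.143 | 15.4% |
| 0.35 | 0 | 0.10 | 0.10 | 0 | 0.035 | – | 5.5% |
| 0.70 | 0 | 0.10 | 0.10 | 0 | 0.07 | – | 7.7% |
| 0.70 | 0.5 | 0.20 | 0 | 0.35 | 0.8 × 0.35 + 0.14 = 0.42 | 0.417 | – |
| 0.70 | 0.5 | 0.10 | 0.10 | 0.35 | 0.8 × 0.35 + 0.07 = 0.35 | 0.354 | – |
| 0.70 | 1 | 0 | 0.20 | 0.70 | 0.8 × 0.70 = 0.56 | 0.561 | – |

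Under the same random drop-out, observed 9-month data alone gave 0.005 with 5.0% rejection where LOCF gave 15.4% (second row), and 0.701 where LOCF gave 0.561 (last row).

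**Cross-check with another set-up.** With correlation 0.6 and a t-test on change from baseline, all loss late and R = 0, rejection was 7.7% (0.35 SD) and 14.8% (0.70 SD), against 5.2% and 5.5% from observed data. With loss split evenly, LOCF gave 5.7% and 7.8%.

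**Range over the amount lost.** With R = 0 and all loss late, the spurious 9-month difference is 10% of D12 if 10% are lost, 20% if 20% are lost, and 26.5% if 18 of 68 are lost (the loss that would leave the planned 50 per arm).

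**Source of the excess rejection.** In the second-row scenario, one run gave an estimate of 0.144 with standard error 0.153. A shift of 0.144/0.153 = 0.94 standard errors by itself gives about 15.6% rejection. Bias accounts for the whole excess.

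**The case against.** The strongest reply is that the 15% is a corner case. It needs a 0.70 SD effect at week 12, complete loss of that effect by 9 months, and every drop-out occurring after week 12. The protocol's 20% covers the whole 9 months and so includes early loss. With an even split the rate is about 5% to 8%, and if half the gain is kept the two biases cancel. This stands and limits the size of the point. It does not defend the rule, since cancellation would be luck.

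A second reply is that the figures concern a 9-month contrast, whereas the plan names a 3 x 2 ANOVA. This also stands. A real week-12 effect makes the arm-by-time null false, so the rejection rates do not describe that interaction test. They describe the comparison from which maintenance would be read.

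Third, the protocol promises sensitivity analyses, and their methods may sit in a plan not shown. Their brevity is therefore no finding. They leave LOCF as the main analysis all the same.

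Three stronger readings are tempting and not supported:

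- A reader might infer that LOCF standard errors are too small, because single imputation treats filled-in values as observed and the LOCF standard error (0.142 to 0.153) is below that from observed data (0.167). That compares two different estimators. LOCF's reported standard error matched its own sampling SD (0.152 against 0.152), and rejection was about 5% with no effect at any visit.
- A reader might infer that the rule favours the intervention. It does so only if the week-12 advantage fades and enough loss is late. Control-arm values and week-12 declines are carried forward too.
- A reader might infer a separate maintenance endpoint, or that maintenance is the trial's sole purpose. The stated primary objective is effectiveness; maintenance is the stated reason for the longer follow-up.

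**Conclusion.** The concern holds as a matter of bias. The protocol's main missing-data rule assumes an answer to the question the 9-month visit was added to ask, and it can misstate the 9-month arm difference even under completely random drop-out, where the observed data are unbiased.

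The size is p(1 − R)·D12 upwards for late loss, less q·R·D12 for early loss. At 20% loss this runs from a spurious gain of one fifth of the week-12 difference (all late, nothing kept) to the loss of one fifth of a true lasting effect (all early, all kept). The net direction depends on when people leave and on how far the effect fades, and neither is known in advance.

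These figures rest on assumed effect sizes, correlation, drop-out timing and equal random loss in both arms. Drop-out that differs by arm would change them. The point should be fixed, but at its likely size it does not by itself invalidate the trial.

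**What to change.** In Sample Size and Statistical Analysis, replace the LOCF sentence with a likelihood-based linear mixed model for repeated measures, with arm, time and arm by time, using all observed data from all randomised participants. Read the 9-month effect from that model's arm contrast at 9 months. Participants with incomplete follow-up stay in the analysis through the values they have.

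The model assumes data are missing at random. Name multiple imputation with a delta or control-based shift as the sensitivity analysis, to show how far the 9-month result depends on that assumption. Reword the sensitivity sentence so that it asks whether the conclusion changes. Report LOCF only as supplementary, if at all.

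The cost is a change of wording and slightly more analysis work, with no extra data or participant burden. The 9-month interval will be somewhat wider. As a guide, the observed-data standard error of 0.167 is 9% above 0.153 (0.167/0.153 = 1.09) and 18% above 0.142 (0.167/0.142 = 1.18).
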